### Sample size calculation

The main goal of this study is to determine the effect of education on the average score of mental health literacy in two intervention and control groups, which will be analyzed as the difference between the two averages. Since the minimum and maximum score of mental health literacy is between 29 and 130, therefore, the standard deviation of 25.25 points was considered and the number of samples in each group was determined in such a way that with 95% confidence and 80% test power, if the difference between the two averages A score greater than 12 is statistically significant. From the following formulas, the number of participants in each group was stated (Figure 2).

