#### Potential confounds

Researchers anticipate several potential confounds that may influence the outcomes, such as:Pre-existing Mental Health Conditions: Variability in participants’ baseline mental health status may affect their response to the intervention.Socioeconomic Factors: Differences in socioeconomic status might influence participants’ access to mental health resources, potentially impacting outcomes.

The primary outcome of this study is the change in mental health literacy score (MHLS) from baseline to post-intervention and follow-up. The secondary outcome is the change in attitude towards seeking professional psychological help score from baseline to post-intervention and follow-up. Both outcomes will be measured using validated scales.

Demographic and baseline characteristics of the participants will be summarized using descriptive statistics, including mean, standard deviation, median, interquartile range, frequency, and percentage, as appropriate. The normality of the outcome variables will be assessed using graphical methods (histograms and Q-Q plots) and numerical tests (Shapiro–Wilk test). If the outcome variables are normally distributed, parametric tests will be employed; otherwise, non-parametric tests will be utilized.

Between-group differences in outcome variables at post-intervention and follow-up will be analyzed using analysis of covariance (ANCOVA), adjusting for baseline values and other potential confounders. Within-group changes in outcome variables from baseline to post-intervention and follow-up will be analyzed using paired t-tests or Wilcoxon signed-rank tests, depending on the normality assumption. Effect sizes and 95% confidence intervals will be reported for all comparisons.

We will employ techniques such as multilevel modeling (also known as hierarchical linear modeling) or generalized estimating equations (GEE) to model dependencies among observations within the same cluster. The level of significance for all statistical tests will be set at 0.05 (two-sided). All analyses will be conducted using SPSS software version 26.0.

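### The parametric or non-parametric choice hangs on normality of the raw outcome, and conflicts with the unconditional commitments to baseline-adjusted ANCOVA and a cluster model

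*Protocol article*

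**What the plan says.** All the relevant text is in the protocol article, Statistical analysis, under Potential confounds.

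- **The check:** "The normality of the outcome variables will be assessed using graphical methods (histograms and Q-Q plots) and numerical tests (Shapiro–Wilk test"). It is applied to the outcome variables, and no threshold or rule for combining graphs and test is given.
- **The rule:** "If the outcome variables are normally distributed, parametric tests will be employed; otherwise, non-parametric tests will be utilized". It is worded generally and is not confined to any one comparison.
- **Between-group comparison:** it "will be analyzed using analysis of covariance (ANCOVA), adjusting for baseline values and other potential confounders". No normality condition is attached.
- **Within-group change:** it "will be analyzed using paired t-tests or Wilcoxon signed-rank tests, depending on the normality assumption". This is the only place where a non-parametric test is named.
- **Clustering:** the plan commits to "multilevel modeling (also known as hierarchical linear modeling) or generalized estimating equations (GEE) to model dependencies among observations within the same cluster", again without a normality condition.
- **Outcome definition:** the primary outcome is the change in the mental health literacy score from baseline.

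Sampling method assigns whole schools, three per arm, with 102 students per arm.

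**The concern.** Three things are wrong with the rule as written.

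1. **It checks the wrong quantity.** ANCOVA and linear multilevel models make a normality assumption about residuals. A raw outcome can be non-normal with well-behaved residuals, and the reverse. GEE makes no normality assumption at all.
2. **It lets the trial's data select the test.** The selection step is not fully defined.
3. **It contradicts its neighbours.** ANCOVA and a linear multilevel model are parametric. If the check fails, one sentence calls for a non-parametric test while two others call for these models, and the text does not rank them.

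What is at stake is the primary between-group comparison. An ordinary two-group rank test does not use school. It uses baseline only if it is run on change scores. It also does not directly give a mean difference to set against the 12-point target in Sample size calculation.

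**Working it through.** **Inputs from the protocol article.** SD 25.25, difference 12, "with 95% confidence and 80% test power", 30% dropout, three schools and 102 students per arm, two-sided 0.05. The article gives neither a baseline correlation (r) nor an intraclass correlation (ICC). The values of r and ICC below are therefore assumptions, shown as ranges.

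**1. The plan's own sample size.** The normal approximation gives n = 2 × (25.25 × (1.96 + 0.84) / 12)² = 69.5 (with unrounded quantiles), so 70 per arm, and 70 / 0.70 = 100. The t-based version gives 70.5, so 71 per arm, and 71 / 0.70 = 101.4, so 102. The stated 102 is reproduced. It treats students as independent and does not depend on the normality rule. It implies about 71 / 3 = 24 completers per school.

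**2. How easily the check could fail.** Simulated Shapiro-Wilk rejection rates at 5%, mildly skewed data:

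| Skewness | n = 102 | n = 142 |
|---|---|---|
| 0.28 | 14% | 21% |
| 0.40 | 30% | 38% |
| 0.63 | 63% | 77% |

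If six independent checks were made (two outcomes at three time points, an assumption), the chance of at least one false rejection under exact normality is 1 − 0.95⁶ = 26%. These rates describe the numerical test alone. The plan also uses graphs, so they are not the probability of a switch.

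**3. Efficiency if a rank test replaced ANCOVA.** For normal data the rank-sum test has efficiency 3/π = 0.955 relative to the t test on the same variable. This factor multiplies the loss from handling baseline less well.

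- Raw follow-up scores: 0.955 × (1 − r²)
  - r = 0.5: 0.955 × 0.75 = 0.72
  - r = 0.7: 0.955 × 0.51 = 0.49
- Change scores: 0.955 × (1 + r) / 2
  - r = 0.5: 0.955 × 0.75 = 0.72
  - r = 0.7: 0.955 × 0.85 = 0.81

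The efficiency loss is therefore 28% to 51% on raw follow-up scores, and 28% falling to 19% on change scores.

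**4. Type I error if schools are ignored.** With m = 24 per school the design effect is 1 + 23 × ICC. For an unadjusted t test the approximate type I error is P(|Z| > 1.96 / √design effect). The other columns are simulated with 2,000 trials each, three schools per arm and r = 0.5.

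| ICC | Design effect | t test, formula | Rank-sum | ANCOVA ignoring schools | t test on baseline-adjusted school means (4 df) |
|---|---|---|---|---|---|
| 0.01 | 1.23 | 8% | 8% | 8% | 5% |
| 0.02 | 1.46 | 10% | 10% | 13% | 4% |
| 0.05 | 2.15 | 18% | 18% | 23% | 5% |
| 0.10 | 3.30 | 28% | 28% | 32% | 6% |

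The rank test and the t test are inflated alike, and ANCOVA without schools is no better. The cause is leaving out the school, not the use of ranks. The analysis of school means stays near 5%.

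**The case against.** The strongest defence is that the switch was meant only for the within-group comparisons. The normality condition is repeated only there, and the only non-parametric test named is the Wilcoxon signed-rank test. On that reading, between-group ANCOVA and the cluster model stand whatever the outcome's shape. The reading is reasonable and may be what was intended. But the rule is worded generally and comes before both kinds of comparison, so the text does not settle the matter.

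A second defence is that a condensed article leaves the choice of fallback test to the analysis plan. That is fair, and the missing name of a test is not the point here. The point is a rule that is stated, aimed at the wrong quantity, and in conflict with other stated commitments.

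A reader might also infer more than the document supports:

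- **That the non-parametric branch drops both the baseline and the school adjustment.** The article does not say so. Rank-based ANCOVA or a clustered rank test could keep one or both, and a rank test on the change score that defines the primary outcome would use baseline partly.
- **That Shapiro-Wilk alone decides.** Histograms and Q-Q plots are used as well, with no stated threshold.
- **That the switch itself inflates type I error.** The inflation comes from ignoring schools, and a t test suffers equally.
- **That the fallback could never reach significance.** A rank or permutation test on six school values has 20 possible allocations and a minimum two-sided p of 2/20 = 0.10, but no such test is proposed.
- **That no effect estimate would be reported.** The section promises effect sizes and 95% confidence intervals for all comparisons, although an ordinary rank test does not directly supply the adjusted mean difference.

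**Conclusion.** The point holds in a limited form. The plan bases a general choice of test on normality of the raw outcome, which is not what its models assume. It also leaves that rule in conflict with two unconditional modelling commitments. Followed literally, the rule could replace a better primary analysis.

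The size of the harm is conditional on a standard two-group rank test being used. In that case efficiency relative to ANCOVA would be about 0.72 to 0.49 on follow-up scores, or 0.72 to 0.81 on change scores, for an assumed r of 0.5 to 0.7. These efficiencies take normal data and independent students. Type I error would be about 8% to 28% at assumed ICCs of 0.01 to 0.10 with 24 students per school, and that part belongs to ignoring schools. The stated 102 per arm is not affected by the rule. The change should be made, but the text does not show that the primary analysis will in fact lose its adjustments.

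**What to change.** - Delete the normality-based switch for between-group comparisons.
- State one baseline-adjusted, cluster-aware analysis as primary whatever the shape of the outcome, with a small-sample method suited to six schools. Examples are a mixed model with a small-sample degrees-of-freedom correction, or a t test on baseline-adjusted school means with 4 df.
- Check the residuals of that model graphically, without a test that triggers a change of method.
- Use any transformed or rank-based analysis only as a sensitivity analysis named in advance, and have it keep baseline and school.

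The cost is wording in the analysis section. No change to data collection or sample size follows from this point. Trial status describes the trial as still being planned; the edit should be made before any outcome data are examined.

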### Sampling method

This study uses a stratified random sampling method that focuses exclusively on male participants aged 14–20 years. First, a school district is randomly selected from among the available districts. Within the selected district, schools are stratified and then randomly assigned to intervention and control groups. Three schools are assigned to the control group and three schools to the intervention group. A total of 102 male students will be randomly selected from all three schools in each group. The number of participants selected from each school will be proportional to the student population of that school, ensuring fair representation.

Male students were selected for this study due to specific cultural, religious, and logistical constraints. In the study setting, adolescent male students are the primary population with regular and independent access to mobile phones, a key requirement for participation in this digital communication-based intervention. Additionally, the male researcher’s access to female students’ mobile phone numbers is restricted by cultural norms and policies imposed by the Ministry of Education and Culture. These factors make the inclusion of female participants impractical within the framework of this study and necessitate a focus on male students to ensure the feasibility and integrity of the research design.

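### Six schools are randomised, but the plan does not fix whether or how the deciding between-group analysis accounts for school, and some analyses it permits have a type I error well above 5%

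*Protocol article*

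**What the plan says.** On design, the Sampling method section says that "schools are stratified and then randomly assigned to intervention and control groups", and then: "Three schools are assigned to the control group and three schools to the intervention group". Students are sampled inside those schools: "A total of 102 male students will be randomly selected from all three schools in each group". School samples need not be equal: "The number of participants selected from each school will be proportional to the student population of that school".

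On analysis, the Statistical analysis section (under Potential confounds) makes three statements:

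- **Between groups:** "Between-group differences in outcome variables at post-intervention and follow-up will be analyzed using analysis of covariance (ANCOVA), adjusting for baseline values" and other possible confounders. School is not named as a term.
- **Within groups:** changes from baseline "will be analyzed using paired t-tests or Wilcoxon signed-rank tests, depending on the normality assumption".
- **Clustering, in the next paragraph:** "We will employ techniques such as multilevel modeling (also known as hierarchical linear modeling) or generalized estimating equations (GEE) to model dependencies among observations" that share a cluster. The cluster is not defined, and no choice is made between the two techniques.

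The same section moves to non-parametric tests if outcomes are not normally distributed, with no provision for school. All tests are two-sided at 0.05, and 95% confidence intervals are promised for all comparisons. No ICC appears anywhere in the article.

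**The concern.** Because schools are allocated, the comparison of arms rests on six units and carries about 4 degrees of freedom, however many students are measured. A student-level ANCOVA treats some 140 to 200 students as independent. Standard GEE relies on there being many clusters. A multilevel model read against a normal or large-sample reference also understates the uncertainty.

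The protocol names the first method, offers the other two as a choice, and does not say which result decides. Two things are at stake. Ordinary differences between schools could be declared an effect of the intervention. And several admissible analyses with different error rates leave room to choose among them once results are known.

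**Working it through.** **Inputs from the protocol.** Six schools, three per arm. 102 students per arm, so 102/3 = 34 per school on average. With the 30% dropout allowance, 34 × 0.7 ≈ 24 per school. SD: "the standard deviation of 25.25 points was considered", which is (130 − 29)/4. Difference to detect 12 points, 80% power, two-sided 0.05.

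**Assumed.** The ICC, meaning the residual correlation within school after baseline adjustment, is taken over 0.01 to 0.10.

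**The plan's own figure.** The individual-level formula gives n = 2 × [25.25 × (1.96 + 0.84)/12]² = 69.5, so 70 per group. The t-based version gives 71, and 71/0.7 = 101.4, so 102. The stated 102 is therefore reproduced with no design effect, so the sample size treats students as independent.

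**ANCOVA without school.** The design effect is DE = 1 + (m − 1) × ICC, and the true error is 2 × [1 − Φ(1.96/√DE)].

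| ICC | m = 24: DE, error | m = 34: DE, error |
|---|---|---|
| 0.01 | 1.23, 7.7% | 1.33, 8.9% |
| 0.02 | 1.46, 10.5% | 1.66, 12.8% |
| 0.05 | 2.15, 18.1% | 2.65, 22.9% |
| 0.10 | 3.30, 28.1% | 4.30, 34.5% |

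Simulation (10,000 trials per setting) at ICC 0.05 gave 18.3% and 23.1%, and 24.8% with assumed unequal school sizes of 20, 34 and 48 in each arm. At ICC 0 there is no inflation.

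**GEE, uncorrected robust standard error, normal reference, equal schools.** For each arm mean the robust variance is SS/9, where SS is the sum of squared deviations of the three school means. The unbiased variance is (SS/2)/3 = SS/6. The ratio is 6/9 = 2/3, so the standard error is √(2/3) = 0.816 of the right size. The test rejects when |t₄| > 1.96 × 0.816 = 1.60, and P(|t₄| > 1.60) = 18.5%. The ICC does not enter. Simulation gave 18.1% to 19.6% with equal schools and about 20% to 22% with the unequal sizes. The matching interval spans 1.60 correct standard errors each way where t₄ needs 2.78: 1 − 1.60/2.78 = 42% too narrow.

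**Multilevel model.** If the between-school standard error is unbiased but is read against z, the error is P(|t₄| > 1.96) ≈ 12%. This is a calculation for that case, not a simulation of a fitted mixed model.

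**Reference method.** A t test on baseline-adjusted school means with 4 degrees of freedom held 4.7% to 5.6% in every simulated setting (ICC 0 to 0.10).

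**Power of that method, without gain from baseline adjustment, at ICC 0.05.** The variance of a school mean is 25.25² × [0.05 + 0.95/m].

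- m = 34: 637.56 × 0.0779 = 49.7; SE of the difference √(2 × 49.7/3) = 5.76; 12/5.76 = 2.08; power about 36%.
- m = 24: 637.56 × 0.0896 = 57.1; SE 6.17; 12/6.17 = 1.94; power about 32%.

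**The case against.** The strongest reply is that the protocol does commit to modelling dependence within clusters. It says so firmly, after the between-group and within-group tests, and nowhere presents these techniques as an alternative to ANCOVA. Read together, the sentences could describe one baseline-adjusted comparison that includes school. This stands as far as it goes. A reader might infer that the planned test ignores schools and that the trial's error rate is 18%. The document supports neither: ignoring school is one reading, and no single error rate follows from the text.

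The numbers also have limits. The ANCOVA figures depend on an assumed ICC and on how many students are analysed. At ICC 0.05 the 18% figure needs the full 30% dropout, and with all 34 per school, closer to the stated intention-to-treat principle, it is about 23%. The GEE figure has a different cause, the small number of schools, and should not be tied to an ICC. The protocol specifies neither an uncorrected standard error nor a normal reference, so both the GEE and the multilevel figures are conditional on those choices.

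Finally, the model choice and any small-sample correction could sit in an analysis plan that is not shown. Their absence alone would be no finding. What remains is a matter of stated text: ANCOVA is named without school, it is not reconciled with the clustering sentence, and one of the two techniques offered is invalid in its standard form with three schools per arm.

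The within-group tests are secondary. Nothing in the article rests the efficacy claim on them.

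**Conclusion.** The point holds in conditional form. The protocol randomises six schools and leaves the deciding between-group analysis unresolved between an ANCOVA with no school term and an open choice of multilevel model or GEE.

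- If ANCOVA is run without school, the nominal 5% becomes about 8–9%, 18–23% or 28–34% at assumed ICCs of 0.01, 0.05 and 0.10, with 24 to 34 students per school.
- If GEE is run with the uncorrected robust standard error against z, it becomes about 18.5% with equal schools and somewhat more with unequal ones.
- A multilevel model is adequate only with small-sample degrees of freedom. An unbiased standard error read against z gives about 12%.

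The protocol does promise cluster methods, so it cannot be said that the trial will be analysed as if students were independent. The defect is that the text permits that analysis, and others that miss the 5% level, without saying which one counts.

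**What to change.** State one primary between-group analysis before outcome data are analysed. Either of these would do:

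1. A linear mixed model of the MHLS score at the post-baseline assessments, with arm, assessment, arm-by-assessment and baseline MHLS, a random intercept for school and one for student, and the arm effect tested on small-sample degrees of freedom. These are about 4, and fewer if the school strata are modelled; the number of strata is not given.
2. A t test on the six baseline-adjusted school means.

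Remove ANCOVA without school and GEE with uncorrected robust errors as inferential methods. Make any non-parametric fallback respect school as well. Report within-group changes descriptively.

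The edit itself is analysis wording, but the consequences are larger. Intervals become wider, and the planned 80% power does not hold under the valid analysis: roughly 32–36% at an assumed ICC of 0.05. Baseline adjustment may raise this, but the protocol gives no correlation from which to say by how much. The protocol should state this loss openly.

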## Results

### Baseline measures

Before delving into the results, it’s crucial to highlight that these findings are anticipated and based on assumptions, as the study has not been implemented yet.

### Participants’ baseline assessment

At this stage, participants will undergo assessments encompassing mental health literacy (MHL) scores and attitudes towards seeking professional psychological help. Encouragingly, the initial assumptions suggest no notable distinctions between the intervention and control groups at baseline, establishing a solid foundation for future comparisons.

### Anticipated adherence to the intervention

Assuming the successful implementation of the educational intervention, it is expected that participant adherence will be notably high within the intervention group. A majority of participants in this group are anticipated to complete the program, indicating a promising level of engagement and commitment.

### Primary outcome: mental health literacy (MHL)

In accordance with our assumptions, the intervention group is expected to display statistically significant advancements in MHL scores compared to the control group at each assessment juncture (*p* < 0.05). This suggests an anticipated sustained enhancement in MHL among those exposed to the intervention.

### Secondary outcome: attitude toward seeking professional psychological help

The intervention group, as per our hypothetical scenario, is expected to demonstrate a noteworthy improvement compared to the control group at the post-intervention and 3-month follow-up evaluations (*p* < 0.05). However, it is essential to note that, in our assumptions, this positive effect is not expected to endure at the 6-month follow-up. This suggests an anticipated potential necessity for ongoing support mechanisms or booster sessions to uphold the positive shift in attitudes over the long term.

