### Strengths of the study

*Researcher-Developed Intervention:* The study leverages a researcher-developed intervention based on the core components of the Mental Health and High School Curriculum Guide. This enhances the attractiveness and facilitates accurate comparisons with other studies utilizing the Guide.*Use of Social Media Platform:* Instead of traditional face-to-face training, the study capitalizes on the popularity of social media, particularly among students and adolescents. This approach aims to create a more engaging and flexible intervention aligned with students’ free time.*Two Three-Month Follow-Up Phases:* The study’s inclusion of two three-month follow-up phases strengthens its design by assessing the maintenance of intervention results over time.

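### The plan sets out to assess whether the effect lasts, but it names no comparison of the 6-month effect with the 3-month effect, and its anticipated readings infer durability from separate visits

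*Protocol article*

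**What the plan says.** All places are in the protocol article.

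- **Purpose.** Strengths of the study says that the "inclusion of two three-month follow-up phases strengthens its design by assessing the maintenance of intervention results over time".
- **Tests.** Under Statistical analysis (Potential confounds), "Between-group differences in outcome variables at post-intervention and follow-up will be analyzed using analysis of covariance (ANCOVA"), with adjustment for baseline and other covariates. Within-group changes from baseline get paired tests. Multilevel modelling or GEE is named for dependence within clusters. Effect sizes and 95% confidence intervals are promised for all comparisons. On alpha: "The level of significance for all statistical tests will be set at 0.05 (two-sided"). No arm-by-visit term and no contrast between the two follow-ups is named.
- **Anticipated reading, literacy.** Significance at every assessment is expected, and then: "This suggests an anticipated sustained enhancement in MHL among those exposed to the intervention".
- **Anticipated reading, attitude.** Improvement with p < 0.05 is expected at post-intervention and 3 months, but "in our assumptions, this positive effect is not expected to endure at the 6-month follow-up". The next sentence reads: "This suggests an anticipated potential necessity for ongoing support mechanisms or booster sessions to uphold the positive shift in attitudes over the long term".
- **Abstract.** Its Results paragraph expects the reverse for attitude: a benefit at 6 months and none at 3 months.

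**The concern.** Whether an effect has faded is a question about the difference between two between-group effects, one at 3 months and one at 6. The named tests ask something else: whether each effect, taken alone, differs from zero. A constant effect can pass at one visit and fail at the next by chance. In the other direction, an effect that has halved can still be significant at both visits and be called sustained.

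The trial could therefore report fading of the attitude effect, with a suggestion of boosters, when nothing has changed. It could equally report lasting literacy gains when much of the gain has gone. The article addresses policymakers and educators, so durability is one of the messages likely to be used.

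**Working it through.** **1. The plan's own sample size.** Sample size calculation gives a difference of 12 points, says "the standard deviation of 25.25 points was considered", and plans "with 95% confidence and 80% test power". Then n per arm = 2 × [(1.960 + 0.842) × 25.25 / 12]² = 69.5; the t-test version gives 70.5, rounded up to 71. With 30% loss, 71 / 0.70 = 101.4, so 102. The stated figure is reproduced, and it contains no allowance for schools. The target is 12 / 25.25 = 0.475 SD.

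**2. Inputs for the 6-month test.** From the document: 102 × 0.70 ≈ 71 completers per arm, three schools per arm, two-sided 0.05. Assumed, because the document gives no value: a true constant effect of 0.5 SD (no SD or target is stated for the attitude scale), school ICC 0.01 to 0.05, baseline correlation r and between-visit correlation ρ.

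**3. Chance that the 6-month test misses a lasting 0.5-SD effect.** In SD units, SE = √{2 × [ICC/3 + (1 − ICC)/71]}.

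- Ignoring schools: SE = √(2/71) = 0.168; 0.5 / 0.168 = 2.98 against 1.96, so the miss rate is 15%.
- Six schools, t on 4 df (critical value 2.776). At ICC 0.02, SE = √[2 × (0.00667 + 0.01380)] = 0.202, noncentrality 2.47, miss rate 53%.

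| Setting (4 df) | ICC 0.01 | ICC 0.02 | ICC 0.05 |
|---|---|---|---|
| No baseline gain | 47% | 53% | 65% |
| r = 0.5, student-level variance only × (1 − r²) | 38% | 46% | 62% |
| r = 0.5, both levels × (1 − r²) | 35% | 42% | 56% |
| r = 0.7, student-level variance only | 26% | 38% | 58% |
| r = 0.7, both levels | 20% | 26% | 42% |

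For 0.475 SD without baseline gain the miss rates are 19% ignoring schools, and 51%, 57% and 68% at the three ICCs.

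**4. How often an unchanged effect looks as if it faded.** School means were simulated at two visits with an exactly constant effect (400,000 runs per setting, 4 df, no baseline gain, ICC 0.01-0.05, ρ 0.5-0.7). Significant at 3 months but not at 6 occurred in 13-19% of trials for effects of 0.475-0.5 SD. Among trials significant at 3 months, a constant 0.5-SD effect was non-significant at 6 months in 28-50%. Ignoring schools, the pattern occurs in about 7-9% of trials at 0.5 SD.

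**5. The direct contrast under the same assumptions.** The 6-minus-3-month contrast has SE × √[2(1 − ρ)]. With a constant effect it points wrongly to fading in 2.5% of trials. Its power is limited. It misses complete loss of a 0.5-SD effect in 47-65% of trials at ρ = 0.5 and 26-48% at ρ = 0.7, and it misses loss of half the effect in 73-88%.

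**The case against.** **No rule is stated.** A reader might infer that a non-significant 6-month test is the criterion for an effect that did not last. The text does not say so. The Results section opens by calling its findings anticipated and assumption-based, the attitude paragraph is hedged, and it attaches no p-value to 6 months. The abstract gives the opposite pattern. This objection stands: the passages show how results might be read and fix no decision rule.

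**The power figure is not fixed by the documents.** A reader might also infer that the 6-month test misses a lasting effect about half the time. On the document's own inputs the figure is 15%. Values near half need an assumed ICC, a 4-df reference that the plan does not specify and, at the lowest ICCs, no gain from the baseline adjustment that the plan does specify. This stands too, so only a range can be given. On the other hand, schools are the unit assigned and the plan undertakes to model clusters, so 15% does not describe the clustered analysis either.

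**The SAP may cover it, and intervals are promised.** An arm-by-visit contrast could be left to an analysis plan. But the article itself names the tests and the inferences, and these tests cannot carry these inferences. An interval at each visit is not an interval for the change between visits.

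**The contrast is weak and shows shrinkage only.** Both are true. An interval below zero would support a statement that the effect diminished, but not that it is absent.

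**Conclusion.** The point holds in a limited form. Maintenance is a stated purpose, no comparison of the two follow-up effects is named, and the only readings on offer go visit by visit. That mismatch does not depend on power.

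Its size does depend on assumptions. With 71 completers per arm and a constant 0.5-SD effect, the 6-month test misses about 15% of the time ignoring schools. With six schools on 4 df and ICC 0.01-0.05, it misses 47-65% without baseline gain and about 20-62% with a baseline correlation of 0.5-0.7. An apparent fade with nothing changed occurs in about 13-19% of trials (4 df, no baseline gain, 0.475-0.5 SD, ρ 0.5-0.7). The ICC, the correlations and the attitude effect size are assumed throughout.

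The change should be made, but the point concerns interpretation, mainly of a secondary outcome. It does not undermine the primary between-group comparison.

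**What to change.** - **Statistical analysis.** For each outcome, fit one baseline-adjusted model over the follow-up visits that accounts for school and for repeated measures within student, with an arm-by-visit term. Report the 6-minus-3-month difference in the between-group effect with its 95% confidence interval, beside the 6-month effect and its interval.
- **Anticipated results for both outcomes.** Base durability statements on these two intervals together. A contrast interval wholly below zero supports saying that the effect diminished. A non-significant 6-month test alone is reported as inconclusive, and not as fading or as support for boosters.
- **Abstract and Results.** Reconcile the opposite 3- and 6-month expectations for attitude.

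**Cost.** No new data or participants are needed, since the 3- and 6-month questionnaires are already scheduled. The work is more than a change of wording: multilevel modelling or GEE is at present named only for clustering, so the repeated-measures structure must be added and specified. With six schools the contrast will often be imprecise, and durability may have to be reported as uncertain.
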